### Ethics and dissemination

The study has been approved by the Medical Ethics Committee of Amsterdam University Medical Centers, University of Amsterdam (2019_101), the competent authority Central Committee on Research Involving Human Subjects (Centrale Commissie Mensgebonden Onderzoek) and the ethics committees of the participating hospitals. All treatments are based on best evidence and expected to benefit participants. Because all treatments are well-known procedures and the trial cannot be blinded, no data management committee will be required. Detailed monitoring procedures will be described in a study-specific monitoring plan.

The results of research will be submitted for publication to peer-reviewed scientific journals and both positive and negative findings will be disclosed, unreservedly. There are no restrictions placed upon publication by the sponsor of this study (Hospital Gelderse Vallei, Ede, the Netherlands).

This study will be conducted according to the principles of the Declaration of Helsinki (Version October 2013, adopted at the 64th WMA General Assembly, Fortaleza, Brazil) and in accordance with the Medical Research Involving Human Subjects Act (WMO). Guideline for Good Clinical Practice (ICH-GCP); the Dutch Medicines Act and the Dutch data protection regulation.

Only the principal investigator and dedicated research assistants will be able to access the source data. Data will be kept for 15 years. After that, the data will be anonymized (keyfiles destroyed).

The data will be coded in such a way that they cannot directly be traced back to the identity of the participant. Only the project leader and primary researcher have access to the key file with codes and participant data. Codes and participant data will be stored in password-protected files. After finishing the study, the key to the code will be safeguarded by the coordinating investigator.

## Discussion

This study protocol, which adheres to SPIRIT 2013 [64], describes the first randomized controlled trial evaluating whether AM is non-inferior to first choice treatment for insomnia CBT-I in treating insomnia in patients with medical conditions. The results will offer valuable data about the efficacy of treatments for insomnia in patients with a chronic medical condition.

This study has some limitations. First, neither the practitioner nor the participants can be blinded to allocation. Second, patients with strong preferences for one of the treatments (e.g., AM or CBT-I) may be less willing to participate in the study as randomization can allocate them to the non-preferred treatment. Therefore, we will assess treatment preference and explore its effect on the primary and secondary outcomes. Furthermore, we will assess drop out after randomization. Third, due to the potential drug-drug interactions for amitriptyline, patients using psychopharmaceuticals (other than benzodiazepines) are excluded from the study. The use of psychopharmaceuticals can be related to more severe disease burden. This might result in an underrepresentation of patients with severe disease burden. Fourth, in the present study, we focus on the non-inferiority of both treatments. If shown to been non-inferior, future research should include a cost analysis to compare the economic impact of both treatments

The results of this trial will be of clinical relevance in the treatment of insomnia for patients with long term medical conditions. If the results do not show low-dose amitriptyline is as effective as CBT-I, CBT-I will remain first choice treatment especially in this relative fragile population with comorbid medical conditions. On the other hand, if the results indeed demonstrate that both interventions lead to a similar reduction of insomnia and comparable treatment evaluation, an effective, safe, and low-cost alternative pharmacological treatment will become available for chronic insomnia patients with a long term medical condition. The results can also provide insights in effects of both treatments on daytime symptoms, so patients and caregivers can be adequately informed in order to decide which treatment to choose. Furthermore, the pharmacological treatment option might prevent (new) insomnia patients becoming dependent on benzodiazepines. Research on mediators is valuable for improving knowledge of the working mechanisms of a treatment that will lead to therapeutic change. In turn, these elements can be intensified and refined, which can make treatment more effective and less costly. Identifying moderators of treatment outcome enables the tailoring of treatment options (psychological or pharmacological treatment) to individual patients.

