### Secondary objective

Secondary objectives include to evaluate 1) relapse in insomnia rates in both groups up to 12 months post treatment, 2) secondary outcomes after 12 weeks and 12 months of treatment (sleep quality, fatigue, pain, depression, anxiety, physical functioning, impairment of functioning), 3) treatment evaluation (side-effects, adherence and withdrawal), and 4) possible mediators and moderators of treatment outcome.

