### Treatment evaluation

Adherence to CBT-I is assessed by a 5 item self-constructed questionnaire. This questionnaire assesses on a 5-point scale the extent to which participants followed each of their 6 treatment instructions (e.g., sleep hygiene advices, relaxation, use of sleep diary, sleep restriction and/or stimulus control, worry program and thought diary) since their prior visit. Item scores are added and the range of the total score is between 5 and 25. A higher score represents a better adherence. Furthermore, the number of missed sessions per participant will be tracked.

Treatment adherence to medication will be measured by pill count and a questionnaire (the Medication Adherence Rating Scale (MARS-5) [50] at 12 weeks. The MARS-5, a self-report instrument, contains 5 items regarding medication adherence. Each item is rated on a 5-point Likert scale, and the range of the total score is between 5 and 25. A higher score represents better medication adherence. Adherence by pill count will be calculated by the number of tablets provided minus the number of tablets returned to the investigator or reported as lost divided by the number of days on the study (correcting for dose) multiplied by 100.

Side-effects (including daytime sleepiness) are measured with the Antidepressant Side-Effect Checklist (ASEC) [52], which consists of 21 symptom items scored on a 4-point scale. An additional item asks whether the patient believes this symptom is linked to the treatment. Room for comments and additional side-effects is provided and three additional symptoms are asked. For this study, we split symptom 2 “Drowsiness” into “difficulty waking up/drowsiness when waking up” and “drowsiness during the day.” Symptom 3 “Insomnia” (difficulty sleeping) was split in “vivid dreams” and “disturbed sleep” as these might be side-effects of the treatment. The number, type, and severity of symptoms and their assumed link to treatment will be used to describe the experienced side effects. Daytime sleepiness (as a symptom) is measured by the Epworth Sleepiness Scale (ESS) [53]. The ESS is a 8-item questionnaire (scores 0–24) that requires participants to indicate how likely they would be to fall asleep or doze in various situations. ESS scores > 10 are considered to indicate excessive levels of daytime sleepiness.

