For the AM group, withdrawal from medication will be measured with the 43-item Discontinuation-Emergent Signs and Symptoms (DESS) checklist [54], adjusted to self-administration format. Participants will be asked whether they have newly experienced one of the listed signs or symptoms during the first week after they have discontinued the treatment. The number of newly occurring events will be used to measure the effect of discontinuation.

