### Sample size

We hypothesize that the effect of low-dose AM at 12 weeks is non-inferior to the golden standard CBT-I. A low-dose AM will be considered non-inferior to CBT if the mean post treatment ISI total score does not exceed that of the CBT-I group by more than 4 points, i.e., 50% of the minimum clinical significant difference reported following CBT-I. The standard deviation of the ISI in our study is assumed 4.4 [61]. Sample size determination following the recommendations outlined in Tamayo-Sarver et al. [62] using a one-tailed test and a 5% significance level showed that 84 participants in each group will provide adequate power (90%) to reject the null hypothesis that the ISI change produced by low-dose amitriptyline is not similar to those produced by CBT-I. The dropout rate is estimated to be 13% [41]. Hence, 190 participants in total will be included.

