The primary analysis will be conducted according to intention-to-treat, i.e., all randomized patients are included and are analyzed in their randomly assigned treatment group. We will use multiple imputations to handle missing data for outcomes that are based on the measurement at a single time point, including the primary outcome of the ISI score at week 12. We will include all baseline demographic and clinical characteristics in the imputation model. We will impute a total of five datasets and these will be pooled according to Rubin’s rule [63].

Additionally, the mean ISI score over time will be compared between the two treatment groups using linear mixed models with treatment group (amitriptyline or CBT-I) and time (6 and 12 weeks from baseline) included as fixed effects and ISI score at baseline included as covariate.

We will repeat the ANCOVA and the linear mixed models analysis of the ISI score as a per protocol analysis in which only patients who actually received their assigned treatment (in the CBT-I group attendance of at least 5 out of 7 sessions and in the AM group at least 70 out of 84 days medication) will be included.

Percentages responders until relapse at 2, 4, 6, 8, 10, and 12 months post treatment in both treatment groups will be compared using survival analyses. We will express the difference between amitriptyline and CBT-I in effect sizes and percentage responders. Treatment response is defined as ≥ 8 point reduction on ISI. A relapse is defined as a drawback of ≤ 8 points to the baseline score of the Insomnia Severity Index measured during follow-up at two subsequent measurements.

ANCOVA will be repeated on the secondary outcome measures assessed at week 12 and 12 months, adjusted for the baseline measurement and the linear mixed models will be repeated for the secondary outcomes sleep quality, fatigue, emotional complaints, physical functioning, impairment of functioning, and pain, all assessed at weeks 6 and 12 and 12 months post treatment adjusted for the baseline measurement, according to intention to treat and per protocol analyses. Bonferroni corrections will be applied to the p-values to account for multiple comparisons.

Rates of reported side effects, withdrawal, and rebound symptoms as well as the treatment evaluation items will be described.

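### The Discussion anticipates calling amitriptyline safe on the strength of comparable treatment evaluation, but the planned analysis only describes side effects, and two of the three components cannot be compared between arms

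*Protocol article*

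**What the plan says.** All references are to the protocol article.

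- **Discussion.** If the results demonstrate a similar reduction of insomnia in both arms and "comparable treatment evaluation, an effective, safe, and low-cost alternative pharmacological treatment will become available for chronic insomnia patients".
- **Secondary objective.** The third item defines the term: "treatment evaluation (side-effects, adherence and withdrawal").
- **Statistical analysis.** ANCOVA, mixed models and Bonferroni correction are assigned to the other secondary outcomes. For harms the plan is: "Rates of reported side effects, withdrawal, and rebound symptoms as well as the treatment evaluation items will be described".
- **Treatment evaluation, side effects.** For the ASEC, the number, type and severity of symptoms and "their assumed link to treatment will be used to describe the experienced side effects". The ESS (0–24, above 10 counted as excessive) measures daytime sleepiness. The text restricts neither instrument to one arm.
- **Treatment evaluation, adherence.** "Adherence to CBT-I is assessed by a 5 item self-constructed questionnaire", with missed sessions tracked. Medication adherence is measured by pill count and the MARS-5.
- **Treatment evaluation, withdrawal.** "For the AM group, withdrawal from medication will be measured with the 43-item Discontinuation-Emergent Signs and Symptoms (DESS) checklist".
- **Sample size.** The only margin is on the ISI. Amitriptyline is non-inferior if its mean score "does not exceed that of the CBT-I group by more than 4 points", a margin described as "50% of the minimum clinical significant difference reported following CBT-I".

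**The concern.** The anticipated conclusion has two halves. Effectiveness has a margin, a confidence bound and a sample size. Safety depends on treatment evaluation being comparable, and the text gives that word no meaning: no between-arm estimate and no interval. For adherence and withdrawal, no like-for-like comparison exists by design.

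Two sets of described rates can look alike in a trial of this size while the data remain compatible with a relevant excess on the drug. Both the Background and the Discussion call this population relatively fragile, and the Background gives unsupported off-label exposure as a reason for the trial. A safety statement that the data do not bound would be an unfortunate result.

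**Working it through.** **Step 1. Which components can be compared?**

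| Component | Amitriptyline | CBT-I | Common scale? |
|---|---|---|---|
| Side effects | ASEC, ESS | ASEC, ESS | yes |
| Adherence | pill count, MARS-5 | self-constructed scale, missed sessions | no |
| Withdrawal symptoms | DESS | not measured | no |

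Only the first row, together with adverse events, can support a comparison.

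**Step 2. Numbers per arm.** The protocol gives 84 per arm, 190 in total, 1:1 allocation and 13% dropout. The total reproduces as 168 × 1.13 = 189.84. Randomised per arm: 190/2 = 95. After 13% loss: 95 × 0.87 = 82.65, taken as 82.

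The figure of 84 does not follow from the stated inputs. With SD 4.4, margin 4, one-sided 5% and 90% power, 2 × [4.4 × (1.645 + 1.282)/4]² gives 21 per arm. A margin of 2 gives 83 (84 with the t distribution). That is a separate matter, because 84 and 190 are the sizes the trial will run with. Either way, the size was set on the ISI alone.

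**Step 3. Precision of a difference in proportions.** The protocol gives no side-effect rates, so the rates here are assumptions. With the same rate p in both arms, the 95% half-width is 1.96 × √[2p(1−p)/n].

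| p | n = 82 | n = 95 |
|---|---|---|
| 5% | 1.96 × √(0.095/82) = 6.7 points | 6.2 points |
| 20% | 1.96 × √(0.32/82) = 12.2 points | 11.4 points |

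So even with identical observed rates of 20%, the interval still includes an excess of 11 to 12 points on amitriptyline.

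**Step 4. Power to see a doubling.** This is a yardstick for information content; the protocol plans no such test. Two-sided 5%, pooled variance, p̄ = (p₁+p₂)/2:

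power = Φ{ [|p₂−p₁| − 1.96√(2p̄(1−p̄)/n)] / √[(p₁(1−p₁)+p₂(1−p₂))/n] }

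Example, 10% to 20%, n = 82: (0.100 − 0.1093)/0.0552 = −0.17, so power is 43%.

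| Doubling | n = 82 | n = 84 | n = 95 |
|---|---|---|---|
| 5% to 10% | 23% | 23% | 26% |
| 10% to 20% | 43% | 44% | 49% |
| 15% to 30% | 64% | 65% | 70% |
| 20% to 40% | 80% | 81% | 86% |
| 25% to 50% | 92% | 92% | 95% |

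Power reaches 80% at a comparator rate of about 20% with 84 per arm and 18% with 95. Fisher's exact test is more conservative: at 84 per arm it gives 15% (5 to 10%), 37% (10 to 20%) and 77% (20 to 40%).

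**Step 5. Zero events.** The one-sided 95% upper bound is 1 − 0.05^(1/n): 3.1% for n = 95 and 3.5% for n = 84.

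**The case against.** The strongest case on the other side has four parts.

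1. **The sentence is an outlook.** The Discussion speaks of what would follow if results demonstrate certain things. A reader might infer a formal two-part decision rule, but the documents do not support that: the only decision rule is the ISI margin. Nor does the text equate comparable with a non-significant test; no test of side effects is planned. This stands, and for that reason the power figures above are only a yardstick.

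2. **The size of the blind spot depends on unstated rates.** A reader might infer that the trial would miss a doubling of most side effects. That is unproven. From a comparator rate of about 18 to 20% upward, a doubling is seen with at least 80% power, and the protocol does not say where the rates lie. Severity grades and the ESS score also carry more information than a yes/no outcome.

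3. **Descriptive harms reporting is ordinary, and detail may sit in an analysis plan not shown.** True of the detail. But this article itself fixes description for these outcomes and separately anticipates a conclusion that description cannot carry. The mismatch lies within one document.

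4. **Treatment choice.** A reader might take the safety statement as the stated basis for patients' choices. The Discussion ties choice to effects on daytime symptoms; the safety sentence says only that an alternative will become available.

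What remains is that comparable is undefined, two of its three components cannot be compared, and safe claims more than the planned analysis can deliver.

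**Conclusion.** The point holds as a mismatch between the anticipated safety conclusion and the analysis and instruments meant to support it. It does not touch the primary analysis or its conclusion.

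For the shared measures, the trial can bound a difference in proportions to about ±6 to 7 points at a 5% rate and ±11 to 12 points at a 20% rate. It is unlikely to reveal a doubling of uncommon side effects and cannot rule out event rates below about 3% when none are seen. These figures assume 82 to 95 patients per arm, equal rates for the interval widths, and illustrative rates throughout.

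A reader might infer that a formal non-inferiority margin for safety is missing. None is required, and no allowable excess can be derived from the documents. It would also be demanding at this size: with 20% in both arms and 82 per arm (SE 0.0625), the upper limit of a two-sided 95% interval would fall below a 15-point excess with probability Φ(0.15/0.0625 − 1.96) = 67%, and below a 20-point excess with probability 89%. Reporting the intervals is enough. This is a cheap improvement.

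**What to change.** **Statistical analysis.** For the measures both arms share (ASEC symptoms, ESS above 10, serious adverse events), add the amitriptyline minus CBT-I difference in proportions with a 95% confidence interval. Where an arm has no events, give the exact upper bound. Describe adherence and withdrawal symptoms within each arm, without a claim of comparability.

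**Discussion.** Replace *safe* with tolerability as bounded by these intervals in the patients studied. The last words matter: the exclusion criteria remove listed cardiac conditions, glaucoma and users of psychopharmaceuticals other than benzodiazepines, and the Discussion itself concedes that severe disease burden may be underrepresented.

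**Cost.** A few sentences and a few intervals on measures already planned; no new patients or visits. The only downside is a more cautious safety statement.

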## Trial status

Recruitment is ongoing. Recruitment began in September 2019 in Hospital Gelderse Vallei, Ede, the Netherlands. From November 2020, recruitment started in Hospital Zaans Medical Centre, Zaandam, and Hospital Rivierenland, Tiel, and from June 2021 in Hospital Jeroen Bosch, ‘s-Hertogenbosch, all in the Netherlands as well. At the time of submitting the protocol, 75 of 190 participants (39%) have been consented and 68 randomized. Current protocol version 4.3 is dated August 2020.

## Abbreviations

AM: Amitriptyline
ANCOVA: Analysis of covariance
ASEC: Antidepressant side effect checklist
BZRA: Benzodiazepine receptor agonists
CAM-I: Causal attributions of my insomnia
CBT-I: Cognitive behavioral therapy for insomnia
CIS-20: Checklist individual strength
DBAS: Dysfunctional beliefs and attitude about sleep scale
DESS: Discontinuation-emergent signs and symptoms
DSM-5: Diagnostic and statistical manual of mental disorders 5
ESS: Epworth sleepiness scale
GCP: Good clinical practice
HADS: Hospital anxiety and depression scale
ISI: Insomnia severity index
ITQ: Insomnia type questionnaire
PANAS: Positive and negative affect scale
PSAS: Pre-sleep arousal scale
RCT: Randomized controlled trial
SHS: Subjective happiness scale
SPIRIT: Standard protocol items: recommendations for interventions
SF-36: Short-form 36–item health survey
TPP: Treatment perception and preferences
WSAS: Work and social adjustment scale
